## Abstract

**Background:**

Chronic subdural hematoma (cSDH) is a common neurosurgical condition that is prevalent in elderly patients. There are no well-defined guidelines for cSDH and management strategies vary widely among physicians and institutions, and this variability is expressed in the literature. In general, conservative management is reserved to patients who are asymptomatic or have minor symptoms with mild mass effect. Spontaneous resolution of cSDH is an unusual phenomenon and middle meningeal artery (MMA) embolization seems to reduce the recurrence and progression rate of SDH compared to conventional treatments in multiple cohort studies. A randomized controlled trial is warranted to determine the effectiveness and safety of endovascular embolization for cSDH and whether MMA embolization is superior to conservative management in reducing the progression rate and surgical rescue event.

**Methods:**

This is an Italian multicenter prospective randomized clinical trial with open-label treatment and blinded outcome assessment (PROBE design) to assess the superiority of MMA embolization compared to conservative treatment. A total of 300 patients are planned to be randomized 1:1 to receive MMA embolization (intervention) or conventional treatments (control). The primary outcome is the treatment arm failure which is defined as a composite of incomplete hematoma resolution or surgical rescue within 6 months follow-up. Incomplete hematoma resolution is defined as a reduction of the cSDH thickness ≤50% at follow-up compared to the hematoma thickness measured at the time of randomization. Surgical rescue is intended as hematoma removal for relief or symptoms that developed with continuous growth of the cSDH. In case of bilateral cSDH, the treatment failure occurred when primary outcomes criteria are satisfied for at least one of the two hematomas.

**Discussion:**

This multi-centre randomized controlled trial is needed to evaluate the benefit-to-risk ratio of primary embolization of the MMA to facilitate resolution and prevent rescue surgical evacuation of cSDH. If MMA embolization turns out to be superior to conservative management in this trial, this may prompt further confirmatory trials and, at best, may change clinical practice and guideline recommendations.

**Trial registration:**

ClinicalTrials.gov. Identifier: NCT06274580, Registered on 6 February 2024. This protocol was developed in accordance with the SPIRIT Checklist and by use of the structured study protocol template provided by BMC Trials.

**Supplementary Information:**

The online version contains supplementary material available at 10.1186/s13063-025-09131-y.

## Introduction

### Background and rationale {6a}

Chronic subdural hematoma (cSDH) is among the most common reasons for cranial neurosurgical consult with a reported annual incidence ranges from 14.1 to 20.6 per 100 000 person [1]. It becomes more frequent in elderly patients with an occurrence of 58.1/100000 [2]. Moreover, the wide use of computed tomography (CT) and magnetic resonance imaging (MRI) contributed to increase cSDH detection in the last years.

The pathogenesis of cSDH comprises the formation of fragile capillaries along the subdural neo-membrane encapsulating the blood collection [3]. Risk factors associated with cSDH development are older age, male gender, craniocerebral disproportion, anticoagulation and antiplatelet therapy, bleeding disorder, alcohol abuse, diabetes mellitus and arterial hypertension [4–6]. The cSDH cannot be considered a benign condition, as approximately 30% of patients have a poor prognosis requiring some help at discharge with greater likelihood in aging people [2].

Non-operative management with best medical therapy and serial cranial CT follow-up is the standard treatment for patients affected by cSDH with the following characteristics: a) few symptoms and Markwalder’s Grading Scale-Glasgow Coma Scale (MGS–GCS grade) 0–2 [7]; (b) image showing low mass effect with midline shift less than 1 cm (c) patients having contraindications or refused surgeries [8].

Surgical evacuation (burr-hole drainage or craniotomy) is reserved to patients with symptomatic cSDH having significant mass effect [9].

Natural history of asymptomatic cSDH is not well established and spontaneous resolution of subdural blood collection is reported in literature between 3% and 18% [10, 11]. Several pharmacological therapies have been studied to improve resolution rate, such as corticosteroid [12], angiotensin converting enzyme (ACE) inhibitors [13] and statins [14]. However these reports, have failed to demonstrate their efficacy on hematoma reabsorption with safety concerns [12–14]. With the increasing complexity of the modern patient with cSDH, the embolization of middle meningeal artery (MMA) has emerged as a promising novel treatment. The endovascular approach by eliminating the vascular supply to the subdural neo-membrane seems to reduce progression and recurrence rates of cSDH [15].

Recent systematic review and meta-analyses [16, 17] reported that MMA embolization was associated with lower rates of cSDH recurrence and surgical rescue and higher hematoma resolution rate comparing with conventional treatment.

The randomized trial of endovascular approach (EMBOTRIAL-1) aims to assess the efficacy and safety of MMA embolization over conservative management as primary treatment in patients with cSDH and mild symptoms.

### Objectives {7}

#### Primary objectives

The primary objective of this study is to investigate whether endovascular embolization of MMA is superior in terms of clinical and radiological outcome compared to conservative management.

#### Secondary objectives

Secondary objectives of this study include assessment of:

Endovascular procedure related complications;Neurological deficits;Recurrence rate associated with endovascular embolization of MMA;Resolution rate.

### Trial Design {8}

Embotrial-1 is an Italian multicenter prospective randomized clinical trial with open-label treatment and blinded outcome assessment (PROBE) to assess the superiority of MMA embolization compared to conservative treatment. The intervention group is MMA embolization and comparator control group is the conservative management and best medical treatment. Patients are randomized 1:1. Patient flowchart is depicted in Fig. 1.

**Fig. 1 Fig1:**
[figure not shown]
The flow diagram displays the main study processes, assessments and interventions, including follow-up evaluations

## Methods: participants, interventions and outcomes

### Study setting {9}

The study is not funded. As a quality standard, all the Italian centers involved should meet the following minimum criteria: (1) local tertiary hospital, (2) experience in managing brain trauma or neurovascular disease trials, and (3) could carry out MMA embolization and have more than 30 cases of cSDH every year. Currently, 7 centers (Supplementary material 1) in Italy have been identified for the study. All the clinical investigators are board-certified and have renowned expertise in neurosurgery, neuroradiology and endovascular interventions. The study is open to additional participating neurosurgical centers.

### Eligibility criteria {10}

#### Inclusion criteria

Patients can be included in Embotrial-1 if they meet these criteria:Age over 18 years;No neurological deficits (Markwalder score ≤1);Unilateral or bilateral cSDH;Subdural Hematoma width ≤ 20 mm; midline shift ≤ 7 mm;Independent functional status with mRS score ≤ 2 prior to symptom onset;Written informed consent of the patient to participate in the trial;Likely compliance of the participant in attending follow-up examination.

#### Exclusion criteria

The exclusion criteria are the following:Radiological evidence of an acute or subacute subdural hematoma, subarachnoid hemorrhage, intracerebral hematoma or epidural hematoma;Contraindications to angiography (end stage chronic renal disease, any sign of anatomical variations that could make MMA embolization unsafe, pregnancy);Life expectancy < 1 year;Patients with any kind of ventricular derivation catheter.

### Who will take informed consent? {26a}

Investigators or their representatives being part of Department of Neurosurgery or Department of Radiology and Neuroradiology will have to adequately explain the details of the clinical trial including rationale, design, risks and potential benefits of the study. Patients will be given ample time to think about the opportunity to participate and to discuss the study with their family and their general practitioner. After full and detailed explanation, subjects or their guardians, as well as the investigators, will sign their name and date on the informed consent form.

### Additional consent provisions for collection and use of participant data and biological specimens {26b}

N/A. Biological specimen collections are not needed in this trial.

### Interventions

#### Explanation for the choice of comparators {6b}

Patients assigned to the control group will managed according to the current standard of care with “wait and see” approach and best medical treatment.

#### Intervention description {11a}

Patients randomized to the experimental arm will submit to cerebral angiography and bilateral MMA embolization of the cSHD, even if it is located to only one side. The ipsilateral MMA embolization of the cSDH is allowed when the endovascular procedure cannot be performed on both sides. Patients are preferably under monitored local anesthesia or alternatively under conscious sedation or general anesthesia. Briefly, through femoral or radial artery access a standard 5 French diagnostic catheter is placed in the proximal external carotid artery and a digital subtraction angiography (DSA) is performed. Then, a microcatheter is advanced selectively under roadmap guidance into the main trunk of MMA, and superselective angiography is performed to evaluate for potentially dangerous anastomoses between MMA and ophthalmic or petrous branches prior to embolization [18]. After collateral vessels are excluded, the MMA is occluded with PVA particles (sizes between 40-300µm) or liquid embolizing materials (Onix^®^, Squid^®^, Phil^®^, glue). The successful embolization is defined as that both frontal and parietal branch of MMA are selectively occluded and for this purpose, the microcatheter should be placed as distally as possible. It is recommended to ensure embolic materials penetrating into the capillary network of the dura to be permanently blocked [19]. The use of coils should be avoided because a faster reperfusion via collaterals might be possible.

#### Criteria for discontinuing or modifying allocated interventions {11b}

Patients may withdraw their consent at any time without providing a reason and thus terminate their participation in the study prematurely. Withdrawal from the study and reasons, if known, will be documented. Criteria for premature drop-out include the following: subsequent occurrence of an exclusion criterion, loss of contact, death, and declaration of withdrawn consent.

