### Outcomes {12}

#### Primary Outcomes

The primary outcome is the treatment arm failure which is defined as a composite of incomplete hematoma resolution or surgical rescue within 6 months follow-up. Time zero is defined as the date of randomization for both groups in order to ensure comparability and avoid immortal time bias. For patients randomized to the intervention arm, any surgical rescue occurring after randomization but before the scheduled embolization procedure will be considered a treatment failure, and will be included in the intention-to-treat analysis.

Incomplete hematoma resolution is defined as a reduction of the cSDH thickness ≤50% at follow-up compared to the hematoma thickness measured at the time of randomization.

Surgical rescue is intended as hematoma removal for relief or symptoms that developed with continuous growth of the cSDH.

Symptoms onset were evaluated from clinical investigators at follow-up based on Modified Rankin Scale Score (mRS) [20] and Markwalder scale [7]. In particular, patients with mRS≥3 and Markwalder scale≥2 are candidates to surgical evacuation of cSDH.

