#### Methods in analysis to handle protocol non-adherence and any statistical methods to handle missing data {20c}

The primary analysis will be performed on the intent-to treat set including all randomized patients and based on the treatment arm they were randomized to, regardless of the therapy they actually received. A missing data analysis will be conducted investigating the extent and type of missing values in trial endpoint variables. In case of a suspected non-random missing data mechanism, corresponding sensitivity analyses will be carried out along with a discussion of the results. If suitable, we will consider multiple imputations to full empty cells in the dataset.

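### An exclusion criterion that arises after randomization is a reason to leave the study, so 6-month outcomes would be missing for reasons tied to outcome or arm

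*Protocol article*

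**What the plan says.** All references are to the protocol article.

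- **Drop-out rule.** Section {11b} states: "Criteria for premature drop-out include the following: subsequent occurrence of an exclusion criterion, loss of contact, death, and declaration of withdrawn consent". The same paragraph describes patients who withdraw consent and "thus terminate their participation in the study prematurely". The list therefore reads as grounds for leaving the study, not only for stopping a treatment.
- **Exclusion criteria.** These include "Radiological evidence of an acute or subacute subdural hematoma, subarachnoid hemorrhage, intracerebral hematoma or epidural hematoma" and, among the contraindications to angiography, "any sign of anatomical variations that could make MMA embolization unsafe".
- **Where anatomy is examined.** For the experimental arm, the intervention description {11a} says that "superselective angiography is performed to evaluate for potentially dangerous anastomoses between MMA and ophthalmic or petrous branches prior to embolization". In Table 1, non-contrast CT is the only imaging at screening; DSA appears at t0, alongside randomization and treatment.
- **Primary outcome.** It is a "composite of incomplete hematoma resolution or surgical rescue within 6 months follow-up". Surgical rescue between randomization and embolization is expressly counted as a failure. Death is not mentioned.
- **Analysis.** Section {20c} says: "The primary analysis will be performed on the intent-to treat set including all randomized patients", by assigned arm whatever therapy was received. It promises an examination of missing values and sensitivity analyses if a non-random mechanism is suspected, and adds: "If suitable, we will consider multiple imputations to full empty cells in the dataset".

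**The concern.** An exclusion criterion protects the trial at entry. Applied after randomization, it becomes a rule for removing patients according to what happened to them.

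Two criteria matter here. A new acute or subacute bleed after randomization may be progression of the hematoma or a complication, which is close to what the trial measures. Unsafe anatomy is sought by an angiogram that only the embolization arm is scheduled to have, so control patients with the same anatomy would not be identified and would stay in.

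The primary outcome depends on a 6-month CT. A patient whose participation has ended has no such CT, and the intention-to-treat set would keep that patient without an outcome. Missingness that depends on arm or prognosis is the kind that imputation handles least well. With so few failures expected, a handful of unobserved outcomes can matter.

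**Working it through.** **1. The plan's own sample size.** Inputs from {14}: 10% failure in control, 1% with embolization, two-sided alpha 0.05, power 85%, 10% drop-out. With mean rate 0.055 and difference 0.09:

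n = [1.960·√(2·0.055·0.945) + 1.036·√(0.10·0.90 + 0.01·0.99)]² / 0.09² = 113.7

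Continuity correction: n' = (n/4)·[1 + √(1 + 4/(n·0.09))]² = 134.97, so 135 per arm and 270 in total. Then 270/0.90 = 300, exactly the stated figure. The sizing thus treats drop-outs as contributing no outcome.

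**2. How few failures carry the result.** With 150 per arm, expected failures are 0.01·150 = 1.5 and 0.10·150 = 15, or 16.5 in total. The drop-out allowance is 0.10·300 = 30. That allowance covers all causes in both arms and says nothing about how many would leave by the routes discussed here.

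**3. Anatomy route, moderate case.** Assume a fraction f of the embolization arm cannot be embolized and fails at the control rate of 10%. The intention-to-treat failure rate is (1−f)·0.01 + f·0.10:

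- f = 2%: 1.18%
- f = 5%: 1.45%
- f = 10%: 1.90%

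If these patients are not observed, the arm shows 1%. The distortion favours embolization and is small to moderate.

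**4. Anatomy route, range up to the worst case.** Assume five embolization patients are dropped and the observed result is 1/145 vs 14/150 (Fisher p=0.0008, chi-square p=0.0007). Had all five been followed and k of them failed:

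| k | Embolization vs control | Fisher p | Chi-square p (uncorrected) |
|---|---|---|---|
| 1 | 2/150 vs 14/150 | 0.003 | 0.002 |
| 2 | 3/150 vs 14/150 | 0.010 | 0.006 |
| 3 | 4/150 vs 14/150 | 0.026 | 0.015 |
| 4 | 5/150 vs 14/150 | 0.055 | 0.033 |
| 5 | 6/150 vs 14/150 | 0.103 | 0.064 |

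Up to k = 3 the result stands. At k = 4 the two tests named in {20a} disagree. Only at k = 5 do both lose significance. If each dropped patient failed at 10%, the expected k would be 5·0.10 = 0.5 and the chance of k = 5 would be 0.10⁵ = 0.00001. The last rows therefore need dropped patients to fare far worse than controls.

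**5. Bleeding route, both directions (assumed counts, Fisher).**

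- *Against embolization:* start from 2/150 vs 15/150, p=0.0018. If seven failing control patients leave, the table is 2/150 vs 8/143, p=0.056.
- *For embolization:* with no true effect, 15/150 in each arm. If ten failing embolization patients leave, the table is 5/140 vs 15/150, odds ratio (5/135)/(15/135) = 0.33, p=0.037.

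The sign depends on which arm loses more failing patients, which the document cannot tell us.

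**6. Does the fix need more patients?** No. At 1% vs 10%, power with 135 per arm is about 90%. With all 150 per arm observed it is about 93–94%.

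**The case against.** The strongest reply is that {20c} governs the analysis and keeps every randomized patient by assigned arm, while {11b} never says that drop-outs leave the analysis set. That stands: a reader might infer a flat contradiction with intention to treat, but the text does not go that far. The defect lies one step earlier. The patient stays in the set while the outcome is no longer collected, and no section says that follow-up continues. {20c} does commit to sensitivity analyses, but these can only explore assumptions about scans never taken.

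Second, the anatomy route is an inference. The anatomy was present before randomization, so one may argue that nothing subsequently occurred. {11a} allows one-sided embolization when both sides cannot be done, and a secondary outcome counts successful embolizations, which suggests that failed procedures stay in the trial. This makes the route a natural reading, not a certain one. Yet {11a} gives no path for the patient in whom dangerous anastomoses are found, and {11b} offers one.

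Third, a reader might infer that the rule simply flatters embolization. The bleeding criterion applies to both arms, and the plan expects ten times as many failures in controls, so the net direction is open. Nor are harms erased: {22} requires adverse events to be documented, reported and observed until resolution or a stable condition.

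Fourth, death ends participation whatever the list says, so striking it would change nothing. Whether it counts as failure is a debatable choice that a statistical analysis plan may settle.

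A last reply, that the analysis plan may cover all of this, does not answer the main point. This is a stated rule about ending participation, and no analysis plan can restore data that the protocol stopped collecting.

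**Conclusion.** The concern holds in a limited form. {11b} makes a later exclusion criterion a reason to leave the study. At least one such criterion (intracranial bleeding) is related to outcome, and another (unsafe anatomy) is probably detectable in one arm only. If the rule is followed, the intention-to-treat analysis has informative missing outcomes.

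The size cannot be fixed from the document, which gives no number of patients who would leave this way. Under the moderate assumption that 2–10% of the embolization arm leaves on anatomical grounds and fails at 10%, the observed 1% stands in place of 1.18–1.90%. It is tempting to say that five one-sided drop-outs reverse the trial. That is secure under both tests only if all five fail, and five is itself an assumed number. The anatomy route tends to favour embolization; the bleeding route could go either way.

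The conclusion rests on reading drop-out as leaving the study. The surrounding paragraph supports this, and no other section contradicts it.

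**What to change.** 1. In {11b}, delete the later occurrence of an exclusion criterion as a drop-out reason.
2. In the same section, separate stopping or not receiving the allocated treatment from leaving the study. This concerns data collection only and leaves clinical management to the investigators.
3. State that every randomized patient is followed on the scheduled 3-, 6- and 12-month CTs and visits unless consent to follow-up is withdrawn, contact is lost or the patient dies.
4. Reconcile {11b}, {12} and {20c} so that death before 6 months is not handled as ordinary missing data, for example by a sensitivity analysis that counts it as failure.

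The cost is a wording change and a few more follow-up visits already in Table 1. The sample size need not rise. The article reports 8 patients included by 12 June 2024; the sooner the wording changes, the fewer outcomes can be lost for good.

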#### Strategies to improve adherence to interventions {11c}

To enhance participant adherence to the study, the following strategies were implemented.

Participant training: Clear and accessible instructions will be provided both verbally and in written form at enrollment and prior to each intervention session.Reminders: Email and/or telephone reminders will be sent 24 hours before each intervention session.Support mechanisms: Participants will have access to a study coordinator who will be available to address any questions or concerns related to the intervention.Motivational engagement: Periodic check-ins will incorporate motivational interviewing techniques to support sustained engagement throughout the study.

#### Relevant concomitant care permitted or prohibited during the trial {11d}

Patients in both groups are treated according to the currently established standard of care at the trial center. Any concomitant care as part of routine clinical practice is permitted.

#### Provisions for post-trial care {30}

A proband cover for all patients participating in the study is contracted to compensate for trial-associated harm occurring within 3 years of trial participants’ final study visit.

### Outcomes {12}

#### Primary Outcomes

The primary outcome is the treatment arm failure which is defined as a composite of incomplete hematoma resolution or surgical rescue within 6 months follow-up. Time zero is defined as the date of randomization for both groups in order to ensure comparability and avoid immortal time bias. For patients randomized to the intervention arm, any surgical rescue occurring after randomization but before the scheduled embolization procedure will be considered a treatment failure, and will be included in the intention-to-treat analysis.

Incomplete hematoma resolution is defined as a reduction of the cSDH thickness ≤50% at follow-up compared to the hematoma thickness measured at the time of randomization.

Surgical rescue is intended as hematoma removal for relief or symptoms that developed with continuous growth of the cSDH.

Symptoms onset were evaluated from clinical investigators at follow-up based on Modified Rankin Scale Score (mRS) [20] and Markwalder scale [7]. In particular, patients with mRS≥3 and Markwalder scale≥2 are candidates to surgical evacuation of cSDH.

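### A control patient who is embolized can count as a success of conservative management if the hematoma then shrinks by more than 50%, because the primary outcome has no rule for embolization outside allocation

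*Protocol article*

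**What the plan says.** Under Primary Outcomes, treatment failure is a "composite of incomplete hematoma resolution or surgical rescue within 6 months follow-up". The two components are then defined:

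- Radiological: "Incomplete hematoma resolution is defined as a reduction of the cSDH thickness ≤50% at follow-up", relative to thickness at randomization. The text does not say whether the 3-month scan, the 6-month scan or either one decides.
- Surgical: "Surgical rescue is intended as hematoma removal for relief or symptoms that developed with continuous growth of the cSDH".

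Five other sections bear on a control patient who is embolized:

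- Trial Design {8}: the "comparator control group is the conservative management and best medical treatment".
- Section {11d}, the place for permitted and prohibited care, prohibits nothing: "Any concomitant care as part of routine clinical practice is permitted".
- Study setting {9}: each center must be one that "could carry out MMA embolization and have more than 30 cases of cSDH every year".
- Section {11b}: the drop-out criteria are "subsequent occurrence of an exclusion criterion, loss of contact, death, and declaration of withdrawn consent". Receiving the other arm's treatment is not among them.
- Section {20c}: patients are analysed in the arm they were randomized to, "regardless of the therapy they actually received".

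Primary Outcomes does rule on one event of this kind: surgical rescue in the intervention arm before the scheduled embolization is a failure. It has no matching rule for embolization of a control patient.

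**The concern.** The trial compares embolization with conservative management, and physicians and patients know the allocation. Suppose a control hematoma grows, the patient is embolized at the same center, and by the deciding scan thickness is less than half its value at randomization. Conservative management did not resolve the hematoma, yet neither failure component is met. The result of the experimental treatment is then credited to the comparator.

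Each such patient removes a failure from the control arm, so the observed difference shrinks and power falls. Few failures are expected, so a handful of patients matters. Repeat embolization in the intervention arm is not scored either; that gap could work in the other direction.

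**Working it through.** **1. Scoring a control patient embolized within 6 months, under the text as it stands**

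| Situation | Surgical component | Thickness component | Score |
|---|---|---|---|
| Reduction of 50% or less at the deciding scan | not met | met | failure |
| Reduction above 50% at 6 months; only the 6-month scan decides | not met | not met | success |
| Growth seen at 3 months, reduction above 50% at 6 months; either scan decides | not met | met at 3 months | failure |
| Growth found on an unscheduled scan before 3 months, reduction above 50% at the scheduled scans | not met | not met, if only scheduled scans count | success |

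Table 1 schedules CT at screening and at 3, 6 and 12 months, with none at 1 month, so the fourth situation is possible. Intention-to-treat fixes the arm in which the patient is counted. It does not say whether the embolization is an event.

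**2. The plan's sample size**

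Inputs from Sample size {14}: 1% versus 10%, two-sided alpha 0.05, power 85%, 10% drop-out, 300 in total. Allocation is 1:1 (Trial Design {8}). The mean rate is 0.055.

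- Uncorrected: n0 = [1.960·√(2·0.055·0.945) + 1.036·√(0.10·0.90 + 0.01·0.99)]² / 0.09² = 113.7 per arm.
- With continuity correction: n = (n0/4)·[1 + √(1 + 4/(n0·0.09))]² = 134.97, so 135 per arm.
- With drop-out: 135/0.90 = 150 per arm, 300 in total.

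The stated 300 reproduces exactly, so the sample size calculation is not in error.

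**3. What masking would cost**

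Let f be the share of would-be control failures who are embolized and then pass the thickness criterion. The control rate becomes 10%·(1 − f). The article gives no value for f, so those below are assumptions. Exact power sums the binomial probabilities of all outcome pairs, with 135 per arm and 1% in the intervention arm, for which the test is significant at 5% in favour of embolization. Both tests are shown because section {20a} allows either.

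| f (assumed) | Control rate | Chi-square power | Fisher power |
|---|---|---|---|
| 0 | 10% | 94.8% | 90.4% |
| 10% | 9% | 90.8% | 84.3% |
| 20% | 8% | 84.6% | 75.5% |
| 33% | 6.7% | 71.6% | 59.3% |
| 50% | 5% | 48.7% | 33.9% |

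The plan expects 135 × 0.10 = 13.5 control failures, so f = 20% is about 2.7 patients. Power falls below the planned 85% at about 10% masking with Fisher's test and at about 20% with the chi-square test.

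**The case against.** Five arguments stand against the point, and each limits it.

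- **A reader might infer that every embolized control is scored as a success.** The text does not support that. The thickness criterion applies whatever treatment was given, and if the 3-month scan can decide, growth seen there is already a failure.
- **A reader might infer that the protocol provides for embolization of controls.** It does not. Control care is described as watchful waiting with best medical treatment, embolization is described only for the experimental arm, and surgical evacuation is the step named for patients who worsen. Centers in such a trial need the capability anyway. What stands is that section {11d} excludes nothing and no scoring rule exists, so the route is left open.
- **The power figures rest on assumed shares.** They show sensitivity, not expected harm. The planned 10% is also below the control failure and progression rates cited in Sample size {14} (11% to 27.5%, 17%, 83.6%). From 17%, masking half leaves 8.5%, with exact power of about 88% (Fisher 80%).
- **Analysis as randomized, with crossover ignored, is a legitimate choice.** Dilution is conservative for a superiority claim. Scoring an open-label decision as failure could inflate control failures, which is the anti-conservative direction. This stands, and it is why the current definition should be reported alongside. The composite already contains one open-label decision, the operation.
- **The full protocol and analysis plan are not shown.** Data fields and sensitivity analyses may be there. The endpoint definition, however, is set out in the article, down to the mirror case in the intervention arm, so the missing rule is a gap in a stated definition.

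**Conclusion.** The point holds conditionally. As the primary outcome is written, a control patient embolized within 6 months for growth or symptoms can count as a success of conservative management if thickness at the deciding scan has fallen by more than 50%. For the control arm, the bias is toward no difference.

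Its size is unknown. Assuming 10%, 20% and 33% of control failures are masked, 135 evaluable per arm and 1% in the intervention arm, exact chi-square power goes from about 95% to 91%, 85% and 72% (Fisher from 90% to 84%, 76% and 59%). The documents do not support a claim that the trial is underpowered or that crossover will be common. The definition should be changed because doing so is cheap and few events are expected.

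**What to change.** In Primary Outcomes:

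1. Count as treatment failure any non-allocated MMA embolization in a control patient, or repeat embolization in an intervention patient, within 6 months of randomization, when hematoma growth is documented on blinded CT or new symptoms are documented.
2. State which CT (3-month, 6-month or either) decides incomplete resolution.
3. Record the date and reason of each such embolization.
4. Report as a sensitivity analysis the current definition, under which embolization is not itself a failure, with patients analysed as randomized.

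The cost is about two sentences in the outcome definition and a small addition to the eCRF. A scan that prompts such an embolization would also need to go to the blinded reader. At the last reported status 8 of 300 patients had been included. The downside is that an open-label decision enters the endpoint; the documentation requirement and the sensitivity analysis limit this. The change concerns scoring only and sets no rule on whether control patients may be embolized.
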